***Description of FAM-CARE Service Program***

EGPAF-Swaziland is piloting a FAM-CARE program, implemented with program funding prior to initiation of the current study. Viral load monitoring is in the process of being implemented at all HIV care sites in Swaziland. For implementation of the FAM-CARE program, EGPAF-Swaziland has randomly selected one hospital and one health center and its cluster clinics (Emkhuzweni cluster and Pigg’s Peak cluster) as FAM-CARE sites and one hospital and one health center and its filter clinics (Dvokolwako cluster and Mbabane cluster) which continue their current standard of HIV care (separate pediatric and adult HIV clinics) and serve as control comparison sites. A brief description of the FAM-CARE program that has been implemented at the selected sites is provided below.

*Enrollment of patients into the FAM-CARE program*

Children receiving HIV care and treatment services at the selected FAM-CARE facilities will be the primary starting point for identifying other HIV-positive family members to be enrolled into care. The children will be recruited primarily from the HIV care and treatment departments, and in any other units within the health facility such as maternal/child health programs or PMTCT follow-up programs. After identifying a child receiving HIV treatment services, the health care worker will talk to the mother or caregiver about the FAM-CARE program within the health facility.

The adult who has brought the child to the facility will be asked the following questions:

1. If they are also HIV-positive and receiving care and treatment services. If yes, they would be invited to participate in the FAM-CARE initiative at the facility.
2. If any of their family members (spouse, children etc.) are also HIV-positive and receiving care and treatments services. If yes, an invitation letter will be issued inviting all family members to come to the health facility to participate in the FAM-CARE program at the facility if feasible. If needed, the facility health care workers will facilitate transfer out from other facilities for family members receiving HIV care at another facility. Even if the family members are not on ART but are known to be HIV-positive, they will be invited to participate in the FAM-CARE program.
3. If any of their family members (spouse, children etc.) have not tested for HIV in the past year. If yes, an invitation letter will be issued inviting all family members to come to the health facility for HIV testing. If any member is found HIV-positive, s/he would be invited to participate in the FAM-CARE program at the facility

Additionally, HIV-positive adults receiving care and treatment services will also be used as index cases to identify HIV-positive children for enrollment into the FAM-CARE program. Each family should have at least one HIV-positive child receiving HIV treatment services.

*Eligibility criteria for enrollment into FAM-CARE program*

- Presence of at least one child (up to the age of 15 years) who is HIV-positive and receiving care at the selected facility. A child will be enrolled if newly diagnosed as HIV-positive and not yet on ART (ART-naïve) or if already known to be HIV-positive but not yet initiated treatment (ART-naïve) or if already on treatment (ART-experienced).
- Family members (someone who is related to the child either by blood or adoption. These can include the mother, father, sister(s) and brother(s), cousins) receiving HIV care and treatment services and residing in the same household as the index child.
- Willingness to disclose HIV status to other family members.

It is estimated that the majority of HIV-positive children will have an HIV-positive family member, but a small percentage may be orphans cared for in a household without other HIV-positive children or adults. Additionally, a small percentage of mothers may not want to participate in the family-centered program because of disclosure issues. We estimate that this will not be more than 10-20% of HIV-positive children. These children would continue their care at the intervention facility but outside of the FAM-CARE program (e.g., routine pediatric or adult HIV clinics).

*Provision of FAM-CARE services*

All family members will be registered in the health facility as a family unit and will have their chronic care files kept in one family folder. Appointments for HIV care and treatment services will be made on the same day for the family as a unit. It is standard for HIV-positive pediatric patients on ART to be seen for monthly visits and ART pick-up. Decisions regarding ART initiation will be based on Swaziland national treatment guidelines.

*Before a scheduled family visit* to the facility, designated health care workers and expert clients (a trained, HIV-positive lay person responsible for educating, counseling, and supporting other HIV-positive clients to understand, manage, and cope with their chronic illness at the health facility level) will pull out the family folder and prepare the ART medication for the family in advance.

*Upon arrival* at the facility, the family will be directed to a designated expert client who will take them to a consultation room where they will receive the required services. Separate consultation for individual family members may be conducted if needed for sensitive topics. In clinics the family will be prioritized over individual clients in order to decrease waiting time, whilst in hospitals or health centers the families will be seen on special days that will be set aside as family-days. If none of the family members is unwell, pre-packed medication will be dispensed by the expert client. However, if a member is unwell, the health care worker will be availed to consult and manage the member. After enrollment into the FAM-CARE program, if the family members are all stable (e.g., virally suppressed on ART), only one family member can visit the health facility to collect the medication for the entire family (except for children who might need dose adjustment based on weight). Other family members will be seen at the health facility only during the stipulated dates for monitoring and as when required. Viral load testing will be conducted on all family members at the same visit (every six months).

*After leaving the facility*, family units will be reminded of their upcoming appointments through text messages three days before the appointment date. If a family unit does not return for their appointment, they will be followed up using routine client follow up processes in the supported facilities.

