
EGPAF has been supporting the Kingdom of Swaziland since 2003 to prevent mother-to-child HIV transmission (PMTCT) and to provide HIV and AIDS care and treatment services to HIV-positive children and adults. Currently, EGPAF-Swaziland supports 66 health facilities in Hhohho and Shiselweni regions of Swaziland with PMTCT, HIV testing and counseling, ART and tuberculosis services. Through PEPFAR funding, EGPAF Swaziland is planning to establish family-centered service delivery program (FAM-CARE) in selected health facilities in the Hhohho region to provide more efficient and effective services to promote better ART initiation and retention in care for adults and children. The roll-out of these services will provide a platform on which to introduce and evaluate routine HIV viral load testing and monitoring in children. Two of four health care clinic clusters in the regimen will be randomized to initiate the new FAM-CARE service delivery platform, allowing a comparison of pediatric retention and viral load suppression between FAM-CARE program and control facilities.

1. **RESEARCH GOALS AND OBJECTIVES**

The overall aim of this study is to demonstrate whether a FAM-CARE approach to HIV care will improve rates of viral suppression and retention of HIV-positive children in care.

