The Hhohho region consists of 4 clinic “clusters”; there was random selection (“coin toss” selection) of “clusters” to initiate FAM-CARE vs to continue standard of care. The FAM-CARE program is being initiated at two “clusters” of clinics that were randomly selected while the other two “clusters” will continue standard of care. The Emkhuzweni and Pigg’s Peak clusters were randomly selected to initiate FAM-CARE, while the Dvokolwako and Mbabane clusters will continue standard of care. For the **prospective** **study evaluation of the FAM-CARE program,** enrollment will take place at selected FAM-CARE and control sites, consisting of the hospital/ health center “parent” of the cluster plus the largest filter clinic for the cluster. Thus, study facilities will include 4 facilities that were randomly assigned to initiate the FAM-CARE program (one hospital plus one filter clinic and one health center and one filter clinic) (FAM-CARE site enrollment) and 4 facilities that were randomly assigned to remain standard of care (one hospital plus one filter clinic and one health center and one filter clinic) (control site enrollment) (see **Table 2** below for facilities/patient numbers). However, we may also expand to include additional filter clinics if necessary.

**Table 2:** Cluster Facilities & Number of Children on ART in Study Facilities

| **Facilities (that have been randomized to FAM-CARE program vs control sites) that will enroll children in the FAM-CARE program evaluation** | | **Children 0-14 Years on ART 31 December 2015** | |
| --- | --- | --- | --- |
| **Facility Name** | **Facility Type** | **Initiated on ART** | **Currently on ART** |
| **Dvokolwako Cluster (Control)** | | | |
| Dvokolwako Health Centre | Health Centre | 32 | 203 |
| Balekane Nazarene Clinic | Clinic | 9 | 36 |
| *Total* |  | *41* | *239* |
| **Mbabane Cluster (Control)** | | | |
| Mbabane Govt | Hospital | 22 | 248 |
| Lobamba ART Clinic | Clinic | 25 | 88 |
| *Total* |  | *47* | *336* |
| **Emkhuzweni Cluster (Intervention)** | | | |
| Mkhuzweni HC | Health Centre | 28 | 159 |
| Mangweni | Clinic | 17 | 64 |
| *Total* |  | *45* | *223* |
| **Pigg's Peak Cluster (Intervention)** | | | |
| Pigg’s Peak Hospital | Hospital | 22 | 318 |
| Horo | Clinic | 3 | 80 |
| *Total* |  | *25* | *398* |

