We will enroll a prospective cohort of HIV-positive children <15 years with at least one additional HIV-positive family member in the household from FAM-CARE and control sites to evaluate the effect of the FAM-CARE program on viral suppression, HIV RNA level >1,000 copies/mL, and retention in care (See **Figure 1**). All HIV-positive children in clinical care, regardless of treatment status or enrollment in the FAM-CARE program, are eligible for enrollment into the study if there is at least one additional HIV-positive family member residing in the household. It is estimated that 85-90% of children in HIV care are currently receiving ART.

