However, there is potential correlation of viral outcomes of children from the same family as well as children from the same facility, thereby violating the assumption of independence required for validity of the chi-square test. We propose to use multilevel generalized linear models to account for the potential intra-cluster correlation due to family unit and facility. In addition, we will adjust for potential confounding that may arise due to imbalances in children’s characteristics between study arms.

b) If the FAM-CARE program decline rate is substantial (>10%) and baseline characteristics of children differ significantly between those who accept FAM-CARE and those who decline, we propose to use the propensity score method to match and compare FAM-CARE and non- FAM-CARE participants. Using data from the FAM-CARE sites, we will estimate the probability of accepting FAM-CARE program given the baseline children and family characteristics. Using special matching algorithms, we will develop a statistical control group that will be compared with the FAM-CARE group. Regression modeling will be used to estimate the effect of the FAM-CARE group compared to the control group.

c) Finally, we will perform an intent-to-treat analysis in which all children at facilities offering the FAM-CARE program will be compared to all children at facilities without FAM-CARE program.

To answer primary aim 2, we will use the same statistical approach described for specific aim 1 above.

To answer secondary objectives 1 and 3, the analysis for the primary objective described above will be repeated using the appropriate outcomes.

To identify factors associated with viral suppression and HIV RNA >1,000 copies/mL (secondary objective 2), we propose to use multilevel logistic regression models to estimate the association between viral suppression and putative factors in each study arm. Examples of factors that might be evaluated include age and gender of child, when ART initiated and ART regimen, serious illness or hospitalization, timeliness of pharmacy drug pick-up, school attendance, family size, number of other HIV-positive individuals in family, HIV treatment and clinical status of other HIV-positive family members, disclosure of HIV status within family.

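### FAM-CARE may predate study enrolment, so for children already in it the modifiable enrolment values are post-exposure, and screening, adjusting or matching on them could remove part of the effect

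*Protocol*

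**What the plan says.** **Timing of the programme.** Under Description of FAM-CARE Service Program the protocol says "EGPAF-Swaziland is piloting a FAM-CARE program, implemented with program funding prior to initiation of the current study", and then "A brief description of the FAM-CARE program that has been implemented at the selected sites is provided below". The Summary of Proposed Research describes the programme as still being set up, and Background and Rationale as planned. The Subject Population section of Data Gathering Activity 1 says "The FAM-CARE program is being initiated at two “clusters” of clinics that were randomly selected". No start date is given, and the Timeline has no line for programme start.

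**Who is enrolled.** "All HIV-positive children in clinical care, regardless of treatment status or enrollment in the FAM-CARE program, are eligible for enrollment into the study", provided another household member is HIV-positive. Nothing restricts entry to families new to FAM-CARE.

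**When values are taken.** Study Procedures and Table 5 tie the first study viral load, the adherence questionnaire, the current regimen and relatives' treatment data to study enrolment. Table 5 lists no date of joining FAM-CARE.

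**How baseline is used.** The Statistical Analysis Plan section identifies baseline characteristics that differ significantly between arms. In option (a) it says "we will adjust for potential confounding that may arise due to imbalances in" children's characteristics between arms. In option (b), used if more than 10% decline and accepters differ significantly from decliners, it says "we will estimate the probability of accepting FAM-CARE program given the baseline children and family characteristics". Option (a) also has an unadjusted chi-square test. Option (c) is an intent-to-treat comparison of all children by facility type.

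**The concern.** A baseline covariate is safe to adjust for because the intervention cannot have changed it. If a family has been in FAM-CARE for some time before the study nurse enrols the child, that no longer holds for variables the programme is meant to improve. An early gain in suppression or adherence would then look like a baseline imbalance. A significance screen tends to select the variables that have moved most, and adjusting for them takes out the part of the effect that runs through them.

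The propensity model has a related problem. It is meant to predict acceptance from what was true beforehand, but for families already in the programme its predictors would be measured after acceptance. Differences that the programme created between accepters and decliners could even help to trigger that analysis.

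At stake are the adjusted estimates for both primary endpoints. The protocol itself says that the chi-square test's independence assumption is violated and proposes multilevel models with adjustment, so these estimates are likely to carry weight.

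**Working it through.** **1. Order of events.** Read literally, Description of FAM-CARE Service Program puts programme start before the study, and the eligibility rule admits children already in the programme. The other sections allow a later start. Even a simultaneous start would leave some prior exposure: enrolment runs over 12 months (Sample size estimation) or three quarters (Timeline), while children on ART generally attend monthly. A child enrolled late could have joined FAM-CARE months earlier. The protocol does not say how many such children there will be or how long they will have been exposed.

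**2. Which values can be affected.** Sex, date of birth and an ART start that precedes FAM-CARE cannot be changed by it. Viral load, adherence, current regimen and relatives' treatment can.

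**3. Is option (b) likely?** Its first condition is a decline rate above 10%. The protocol expects 10-20% of children at FAM-CARE sites to stay outside the programme and plans on 20% refusal, so this condition may well be met. The second condition cannot be foreseen.

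**4. The plan's own figure.** For 80% vs 90% suppression, two-sided alpha 0.05 and 80% power:

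n per arm = [1.96·√(2·0.85·0.15) + 0.842·√(0.80·0.20 + 0.90·0.10)]² / 0.10² = 199, so 398 in total. With 10% loss, 199/0.9 gives 222 per arm and 444 in total. All three agree with Table 3, so the issue is not a numerical error.

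**5. Illustration of the loss.** Let f be the share of the 10-point effect already present at enrolment, and b the within-arm coefficient of month-18 suppression on enrolment suppression. Neither is in the protocol; both are assumptions.

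Adjusted difference = 10 − b × (10·f) points

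| f | b = 0.3 | b = 0.5 | b = 0.7 |
|---|---|---|---|
| 0 | 10 | 10 | 10 |
| 0.25 | 9.25 | 8.75 | 8.25 |
| 0.5 | 8.5 | 7.5 | 6.5 |
| 1.0 | 7.0 | 5.0 | 3.0 |

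For example, f = 0.5 and b = 0.7 gives 10 − 0.7 × 5 = 6.5.

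**6. Would the screen flag it?** With 333 × 0.85 = 283 children on ART per arm, treated as independent, suppression of 85% vs 80% at enrolment gives z = 1.57 and reaches p < 0.05 about 35% of the time. With 87% vs 80%, z = 2.24 and the figure is about 61%.

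**The case against.** **The timing is not settled.** Three sections describe the programme as being set up, planned or being initiated. The Timeline shows intervention SOPs in development through the last quarter of 2016, with enrolment from the second quarter of 2017. This stands. It cannot be said that all enrolment values are post-intervention, only that they are for children already in FAM-CARE. It does not remove the concern, because the eligibility rule and the length of enrolment allow such children under any of these readings.

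**The harmful covariates are not named.** The plan does not list enrolment viral load as an adjuster, and regimen and relatives' treatment appear only as example factors for secondary objective 2. The choice may be left to a statistical analysis plan that is not shown. This also stands. But the screen-and-adjust rule is in the protocol, and it steers towards variables the programme has already shifted. A later plan could not define pre-entry values without entry dates.

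**Join dates may be obtainable.** Table 6 admits caregivers to interview only if they joined FAM-CARE at least 12 months earlier. That suggests the dates can be found, but no study form or Table 5 row is shown to capture them for the whole cohort.

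**Enrolment viral load also captures chance imbalance.** With two clusters per arm, real imbalance is likely, and dropping this covariate leaves some of it uncorrected. This is a true cost, and it argues for keeping an adjusted sensitivity analysis.

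**Conclusion.** The concern holds for children already in FAM-CARE at study enrolment. For them, modifiable enrolment values are post-exposure. Screening and adjusting on such values could remove part of the effect, and the propensity model would condition on covariates measured after acceptance.

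The size is unknown. If half of a 10-point effect is present at enrolment, adjusting for enrolment suppression leaves 8.5 to 6.5 points for coefficients of 0.3 to 0.7. If none is present, or only fixed covariates are used, nothing is lost. The illustration also assumes that the enrolment difference is due to the programme and not to chance differences between clusters.

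A reader might infer that both primary comparisons are biased towards no effect. The documents do not support that. The unadjusted chi-square test and an unadjusted intent-to-treat comparison escape over-adjustment, and no harmful covariate is named. Nor is the 18-month horizon wrong: the objectives define it as time since enrolment. It should simply not be read as 18 months of exposure to FAM-CARE.

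**What to change.** 1. Reconcile the statements on timing and give each facility's FAM-CARE start date.
2. Record each family's join date, and any exit date, on the existing forms.
3. Limit covariates in the adjusted primary model and the propensity model to fixed or pre-entry characteristics: age, sex, ART start date, and pre-entry regimen, CD4 and attendance from the chart abstraction already planned. Give each control facility the start date of its paired intervention facility as reference.
4. Use enrolment viral load as a baseline covariate only in a sensitivity analysis, or in children enrolled at or before FAM-CARE entry.
5. Do not use pre-programme viral loads as a general baseline. The protocol says that testing was mainly confined to suspected treatment failure, so those values are selectively observed.
6. Report the distribution of prior FAM-CARE exposure, and state that the primary result is suppression 18 months after study enrolment among children in care at enrolment.

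The cost is a few form fields and revised analysis wording, with no added visits or participants. The downside is less prognostic adjustment, so some chance imbalance between the four clusters may remain uncorrected.

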**c) Overview Table of Data Gathering Activities**

| **Data Gathering Activities** | Prospective Evaluation of FAM-CARE Program | Qualitative Evaluation |  |
| --- | --- | --- | --- |
|  | Randomized study of sites providing FAM-CARE HIV care compared to control standard HIV care | Semi-structured in-depth interviews |  |
| **Study population** | HIV-positive children and their caregiver  Other HIV-positive adults in the family (not required for enrollment of children) | Caregiver, health care workers |  |
| **Sample size** | 666 HIV-positive children (333 per arm) to achieve the target sample size of 444 HIV-positive children receiving ART from unique families (222 per arm) | Individual interviews with a subset of caregivers (15-25) and health care providers (15-25) in the intervention sites |  |
| **Location of activity** | 8 health care facilities (4 control, 4 intervention) in Hhohho region, Swaziland | 4 health care facilities (intervention sites) in Hhohho region, Swaziland |  |
| **Timing** | Project Month 3 (after IRB submission) | Project Month 18 |  |
| **Method** | Data abstraction from medical records; participant interview; specimen collection | Semi-structured interview led by trained research assistant |  |
| **Informed Consent document** | - Consent form for caregiver-child participation in study cohort - Assent form for children - Consent form for medical record abstraction from HIV-positive adults in the family | - Consent form for interview participation for caregivers - Consent form for interview participation for health care providers. |  |
| **Study Instrument** | Data collection tools include:   - At enrollment:   - Contact form   - Enrollment Forms (caregiver and child)   - Family Clinical Data Abstraction Form   - Child Clinical Data Abstraction Form - At each scheduled follow-up visit:   - Follow-up forms (caregiver and child)   - Family Clinical Data Abstraction Form   - Child Clinical Data Abstraction Form - As needed:   - Missed visit form   - Maternal pregnancy-transfer to MNCH care form   - Child mortality form   - Family member mortality form   - Termination form   - Study viral load specimen tracking form   - Study viral load result form | - Qualitative interview guides for caregivers - Qualitative interview guides for health care providers |  |

1. **Data Gathering Activity 1: Prospective Cohort Enrollment to Evaluate the FAM-CARE Program**
2. **Subject Population**

The Hhohho region consists of 4 clinic “clusters”; there was random selection (“coin toss” selection) of “clusters” to initiate FAM-CARE vs to continue standard of care. The FAM-CARE program is being initiated at two “clusters” of clinics that were randomly selected while the other two “clusters” will continue standard of care. The Emkhuzweni and Pigg’s Peak clusters were randomly selected to initiate FAM-CARE, while the Dvokolwako and Mbabane clusters will continue standard of care. For the **prospective** **study evaluation of the FAM-CARE program,** enrollment will take place at selected FAM-CARE and control sites, consisting of the hospital/ health center “parent” of the cluster plus the largest filter clinic for the cluster. Thus, study facilities will include 4 facilities that were randomly assigned to initiate the FAM-CARE program (one hospital plus one filter clinic and one health center and one filter clinic) (FAM-CARE site enrollment) and 4 facilities that were randomly assigned to remain standard of care (one hospital plus one filter clinic and one health center and one filter clinic) (control site enrollment) (see **Table 2** below for facilities/patient numbers). However, we may also expand to include additional filter clinics if necessary.

**Table 2:** Cluster Facilities & Number of Children on ART in Study Facilities

| **Facilities (that have been randomized to FAM-CARE program vs control sites) that will enroll children in the FAM-CARE program evaluation** | | **Children 0-14 Years on ART 31 December 2015** | |
| --- | --- | --- | --- |
| **Facility Name** | **Facility Type** | **Initiated on ART** | **Currently on ART** |
| **Dvokolwako Cluster (Control)** | | | |
| Dvokolwako Health Centre | Health Centre | 32 | 203 |
| Balekane Nazarene Clinic | Clinic | 9 | 36 |
| *Total* |  | *41* | *239* |
| **Mbabane Cluster (Control)** | | | |
| Mbabane Govt | Hospital | 22 | 248 |
| Lobamba ART Clinic | Clinic | 25 | 88 |
| *Total* |  | *47* | *336* |
| **Emkhuzweni Cluster (Intervention)** | | | |
| Mkhuzweni HC | Health Centre | 28 | 159 |
| Mangweni | Clinic | 17 | 64 |
| *Total* |  | *45* | *223* |
| **Pigg's Peak Cluster (Intervention)** | | | |
| Pigg’s Peak Hospital | Hospital | 22 | 318 |
| Horo | Clinic | 3 | 80 |
| *Total* |  | *25* | *398* |

We will enroll a prospective cohort of HIV-positive children <15 years with at least one additional HIV-positive family member in the household from FAM-CARE and control sites to evaluate the effect of the FAM-CARE program on viral suppression, HIV RNA level >1,000 copies/mL, and retention in care (See **Figure 1**). All HIV-positive children in clinical care, regardless of treatment status or enrollment in the FAM-CARE program, are eligible for enrollment into the study if there is at least one additional HIV-positive family member residing in the household. It is estimated that 85-90% of children in HIV care are currently receiving ART.

